**Secondary outcomes**	
Patient experience	PREM
Absenteeism	Days of sick leave from work
Number of treatments	Numeric
Crossover rate	Numeric

*PROM* patient-reported outcome measure, *PREM* patient-reported experience measure

^a^If inconclusive follow up with an ultrasound or MRI

#### Treatment efficacy

This outcome follows the patient-reported outcome measure-haemorrhoidal impact and satisfaction score (PROM-HISS) questionnaire from the international Delphi procedure of the European Coloproctology group, for which recently the first steps in the validation process were taken [10, 11, 13].

This questionnaire consists of three domains: (1) HD symptoms, (2) impact of HD on daily activities, and (3) satisfaction with treatment [13]. The first domain contains five HD symptoms of which each is scored on a Likert scale ranging from 1 (“not at all”) till 5 (“very much”), resulting in a maximum possible score of 25. During follow-up, any reduction in score on this numeric scale is classified as ‘improvement’. This will then be translated into a binary outcome: “yes” or “no” improvement of symptoms. Both the second and third domains only contain one item, the impact of HD on daily activities and patients’ satisfaction with treatment, respectively. Both are scored on a 10-point numeric rating scale. In respect to the impact of symptoms on daily activities, 0 correlates with “no impact at all” and 10 with “highly impacted on daily activities”. On the contrary, for patient satisfaction with treatment, this ranges between 0 “not at all satisfied” and 10 “very satisfied”. Data from the PROM-HISS questionnaire is collected 1 week after the procedure, so the recall period comprises “the past week” [13].

Complications (i.e. incontinence, abscess, fistula, fissure, urine retention, anal stenosis, arterial bleeding or thrombosed haemorrhoid) are scored at the 6–8 week clinical follow-up appointment at the outpatient clinic. Subjective return of initial symptoms (recurrence) is recorded during the 6-month follow-up period.

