## Introduction

### Background and rationale

Haemorrhoids are a part of normal anatomy, and yet the term haemorrhoids is often used to refer to haemorrhoidal disease (HD) in which clusters of vascular tissue, smooth muscle and connective tissue in the anal canal give rise to symptoms of blood loss, itchiness, soiling and/or prolapse [1]. HD is a common condition with significant epidemiologic and economic relevance. The prevalence of HD rises up to 55% for adults aged between 45 and 65 years of age, with an annual incidence of 5% of the general population [2].

In 1985, Goligher was the first to report a widely accepted grading system for haemorrhoids, which describes four separate groups based on the extent of prolapse inside, or outside, the anal canal [3]. In 460 B.C., Hippocrates described HD with a plethora of treatments, varying from burning, herbs, ligation and surgical excision [4]. Currently, various treatments are available to treat HD [5, 6].

Symptomatic grade 1–2 haemorrhoids can be treated with either rubber band ligation (RBL) or sclerotherapy (SCL) and both treatment options often require multiple sessions [6]. The most common symptom for this patient population is rectal blood loss accompanying defecation [3, 7]. RBL is based on the strangulation and necrosis of haemorrhoidal tissue, resulting in fibrosis and fixation to the surrounding anal mucosa [5, 8]. The most important disadvantages are the feeling of urgency, pain and soiling during and after the procedure. A rare but serious complication of RBL is the occurrence of an arterial bleeding, which in some cases needs to be stopped surgically. On the contrary, SCL induces an inflammation process and local sclerosis of the submucosa which initiates fixation of the haemorrhoidal tissue to the anorectal wall [6, 8]. The haemorrhoid shrinks through the obliteration of the vascular wall. Current literature does not describe major negative side effects, with only a few cases of local infection and haemorrhoidal thrombosis, and very rare complications such as fistula formation and impotence [6, 8]. In the event of haemorrhoidal thrombosis, oral pain medication is usually sufficient; surgical incision of the clot is scarcely required. Another agent that is used in the treatment of HD is phenol. A study showed that it can be equally effective as Aethoxysklerol; however, the use of phenol led to more adverse reactions such as pain, necrosis and ulceration [9].

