	**Tools of measurement**
**Primary outcomes**	
*Patient-related outcomes*	PROM (minimal score 5, maximum score 25): The lower the score the better the result
- Blood loss	Likert scale – 1 (not at all) to 5 (very much)
- Pain	Likert scale – 1 (not at all) to 5 (very much)
- Prolapse	Likert scale – 1 (not at all) to 5 (very much)
- Itching	Likert scale – 1 (not at all) to 5 (very much)
- Soiling	Likert scale – 1 (not at all) to 5 (very much)
	HISS (minimal score 0, maximum score 20)
- Impact on daily activities	Scale – 0 (no impact at all) to 10 (highly impacted on daily activities)
- Satisfaction with treatment	Scale – 0 (not at all satisfied) to 10 (very satisfied)
*Complications*	
Incontinence	Wexner Fecal Incontinence Score
Abscess	Physical examination^a^
Fistulation	Physical examination^a^
Urine retention	Bladder scan
Anal stenosis	Physical examination^a^
Anal fissure	Physical examination
Arterial bleeding	Physical examination
Thrombosed haemorrhoid	Physical examination
*Recurrence*	Subjective return of initial symptoms

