**Primary outcomes**				
HD symptoms (PROM)	X	X	X	X
Abscess			X	
Urine retention			X	
Anal stenosis			X	
Incontinence			X	
Fistula			X	
Recurrence			X	X

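### The closed list of primary complications omits two harms the protocol attributes to sclerotherapy (impotence and local infection), and Table 2 schedules only five of the eight complications listed

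*Protocol article*

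**What the plan says.** The section Treatment efficacy defines the complication outcome: "Complications (i.e. incontinence, abscess, fistula, fissure, urine retention, anal stenosis, arterial bleeding or thrombosed haemorrhoid) are scored at the 6–8 week clinical follow-up". Table 1 gives the same eight items under its primary outcomes.

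Background and rationale describes the harms of each treatment. For SCL, the literature is said to show no major side effects, "with only a few cases of local infection and haemorrhoidal thrombosis, and very rare complications such as fistula formation and impotence". For rubber band ligation (RBL), it says: "The most important disadvantages are the feeling of urgency, pain and soiling during and after the procedure", and also: "A rare but serious complication of RBL is the occurrence of an arterial bleeding".

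Table 2 (Participant timeline) has rows for five complications, all at 6 weeks: abscess, urine retention, anal stenosis, incontinence and fistula.

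Under Statistical analysis, the number of patients with complications is one of two quantities compared between the groups at the interim look.

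**The concern.** The abbreviation *i.e.* makes the list exhaustive. Two harms that the protocol itself links to SCL are not on it. SCL is the arm to be shown non-inferior, with complications named in the hypothesis (Abstract, Discussion), and the Discussion promises to show which treatment gives fewer of them. A patient with new erectile dysfunction, or with a treated local infection that never formed an abscess, would have no complication under the definition as written. Missing such events would make SCL look safer than it is, and the trial could report nothing on a harm it knew of beforehand.

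The second problem is one of consistency. Table 1 and Table 2 sit in the same article and give different content for a primary outcome. This is more than a detail left out of a condensed article.

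**Working it through.** **1. Table 1 and Treatment efficacy against Table 2**

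| Complication | Table 1 and Treatment efficacy | Row in Table 2 |
|---|---|---|
| Incontinence | yes | yes |
| Abscess | yes | yes |
| Fistula | yes | yes |
| Urine retention | yes | yes |
| Anal stenosis | yes | yes |
| Anal fissure | yes | no |
| Arterial bleeding | yes | no |
| Thrombosed haemorrhoid | yes | no |

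Eight items against five, so 3/8 = 37.5% have no row. Of these three, the background names one for RBL (arterial bleeding), one for SCL (thrombosis) and one for neither (fissure).

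**2. Harms named in the background against the list**

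| Harm | Named for | On the complication list | Captured elsewhere |
|---|---|---|---|
| Haemorrhoidal thrombosis | SCL | yes | – |
| Fistula | SCL | yes | – |
| Local infection | SCL | no | partly, through abscess |
| Impotence | SCL | no | nowhere described |
| Arterial bleeding | RBL | yes | – |
| Pain | RBL | no | PROM and PREM |
| Soiling | RBL | no | PROM |
| Urgency | RBL | no | PREM |

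Off the list are 2 of 4 SCL harms and 3 of 4 RBL harms. The three RBL harms are measured by another instrument; impotence is not. The 6-week visit consists of the PROM (five anal symptoms), the Wexner scale and a physical examination. The PREM (Appendix) asks about pain, urge, satisfaction, repeating the treatment and recommending it.

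**3. Possible size**

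The documents give no rate for either omitted harm, so the rates p below are assumptions. With n = 330 SCL patients (Sample size calculation), the expected uncounted events are n × p, and the chance of at least one is 1 − (1 − p)^330.

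| Assumed p | Expected events in 330 | Chance of at least one |
|---|---|---|
| 0.1% | 0.33 | 28% |
| 0.5% | 1.65 | 81% |
| 1% | 3.3 | 96% |
| 2% | 6.6 | 99.9% |

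This applies to a harm possible in every patient. Only men are at risk of impotence. If half were men (an assumption; the sex split is not given), n = 165 and the expected counts halve to between 0.17 and 3.3.

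For scale, the background quotes literature complication rates for SCL of 34–49%, that is 0.34 × 330 = 112 to 0.49 × 330 = 162 patients, under definitions it does not give.

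**4. What recording impotence would allow**

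By the rule of three, no events among 165 men would give an upper 95% bound of about 3/165 = 1.8%. If the question is not asked, no bound can be given.

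**5. Sample size**

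The stated 330 per arm is reproduced from symptom reduction alone (70% in both arms, limit 10%, one-sided 2.5%, power 80%): (1.960 + 0.842)² × 2 × 0.70 × 0.30 / 0.10² = 329.7, rounded up to 330. Complications do not enter it.

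**The case against.** A reader might infer that harms are counted unevenly between the arms. The documents do not support that. One list, one visit and one method apply to every patient, and the Table 2 gap drops one RBL-type harm and one SCL-type harm. Nor can one set two missing SCL harms against no missing serious RBL harm: that compares all SCL harms with only the serious RBL one. Counted alike, more of the named RBL harms are off the list. It would also be wrong to say that no impotence in 330 SCL patients bounds the risk at 0.9%, because the denominator must be men. These points stand.

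The list also follows a stated source, the European core outcome set, and already goes beyond it. That helps less than it seems. Background and rationale presents that set's complications as examples, and the protocol turned them into a closed list, adding the RBL bleed but not these two SCL harms.

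Serious complications and serious adverse events are reported whatever the list says (Data monitoring, Risk of harms), so a serious unlisted event is not lost. But neither impotence nor a treated infection need be classed as serious, and those reports are not said to enter the between-arm count.

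Finally, the case record forms are not shown and may contain an open field, and the interim criterion is not expressly limited to the eight items. Both are true, so actual loss of data is not shown. The published definition still excludes such events, and the two tables still disagree.

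**Conclusion.** The point holds as a modest gap in recording harms for a primary outcome, together with a separate contradiction between two tables. Impotence is the firmer omission, since nothing described would detect a non-serious case; local infection is partly covered by abscess. Any undercount would concern harms that the protocol attributes to SCL, but its numerical effect is probably small: about 0.3 to 6.6 events in 330 under assumed rates of 0.1% to 2%, for harms the protocol calls few or very rare. The main loss is that the trial could not report on a harm it names. The omission of three of eight complications from Table 2 is an inconsistency with no direction. Neither part shows a demonstrated bias towards SCL, and neither affects the sample size.

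**What to change.** - Add local infection and new erectile dysfunction (men) to the complication list in Table 1 and Treatment efficacy, with an open item for any other complication. Ask about all of them alike in both arms at the existing 6-week visit, covering the time since treatment.
- Add anal fissure, arterial bleeding and thrombosed haemorrhoid to Table 2, so that it matches Table 1 and the text.
- State that this one list defines the complication count for both the primary comparison and the interim look.

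The cost is a few extra questions on the case record form, one of them sensitive, and a corrected table. The complication count may rise slightly. No extra visit or examination is needed, and the sample size stays at 330 per arm.

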#### Secondary outcomes

Secondary outcome measures consist of patient experience outcomes (PREMs), number of treatments, crossover and number of days on work leave.

Patient experience outcomes are recorded on the PREM questionnaire (Appendix). It contains a series of questions regarding the patients’ experience of the treatment, which is partly scored on a Likert scale ranging from 1 (“not at all”) till 5 (“very much”). Two additional binary (yes/no) questions are added regarding whether patients would undergo the same treatment and whether they would recommend the treatment to acquaintances suffering from similar HD symptoms. The administration of this questionnaire takes place 1 week after treatment. The total number of treatments, the crossover of treatment arms and days of work leave are recorded after a total of 6 months of follow-up. All data entries are stored in Castor^EDC^.

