### Interventions

Eligible patients are randomised via Castor^EDC^ to either the SCL or RBL arm. Patients who deny randomisation are eligible to the preference arm of their choice. Patients who are randomised to receive SCL are treated with 4 cc Aethoxysklerol 3% (polidocanol) in the haemorrhoidal tissue via a small 18 mm proctoscope (Sapimed). Patients who are randomised to receive RBL are treated via the same small proctoscope with 3 rubber bands which are placed at the base of the haemorrhoidal tissue (Barron ligation). When after approximately 6–8 weeks a second treatment is required this should be the same treatment as the first (SCL or RBL), after which, in case of persistence after at least two treatments and again 6–8 weeks in between treatments, a crossover is permitted. There are no restrictions regarding concomitant care during the trial.

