### Outcomes

#### Primary outcomes

The primary outcome measures are treatment efficacy measured through PROMs according to the ESCP core outcome set of symptom reduction, subjective recurrences and complications (Table 1). The follow-up period for this outcome set is 6 months, and data will be collected at 4 different time points during this period (baseline, 1 week, 6 weeks and 6 months after the first procedure).

**Table 1 Tab1:** Primary and secondary outcome measures

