### Participant timeline

Treatment is provided according to the following timeline (Table 2):T = day 0 → outpatient clinic treatment with either SCL or RBL after providing written informed consent to the treating physician.T = day 7 → telephone appointment with a blinded researcher: the PROM and PREM questionnaires are completed by the researcher.T = 6 → weeks outpatient clinic appointment with a physician. The PROM and Wexner incontinence scale are completed together with a physical examination. If needed, the same treatment (SCL or RBL) is repeated.T = 6 → months telephone appointment with a blinded researcher: PROM questionnaire completed and (subjective) symptoms related to recurrence are assessed.

**Table 2 Tab2:** Participant timeline

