**Secondary outcomes**				
Satisfaction/experience (PREM)		X		
Absenteeism		X	(X)	
Number of treatments			X	X
Crossover rate				X

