For the treatment of grade 1–2 HD, there are several options described in the literature and some of them are relatively new [16–19]. The THROS trial focuses on two less invasive treatment methods and it will provide us with information as to which commonly used treatment method (RBL or SCL) of grade 1–2 HD is the most effective, gives fewer complications and is experienced by the patient as the best option. Considering the available literature on SCL and RBL, we expect the efficacy and complication rates to be equal. However, in most cases of SCL or RBL therapy, repeated procedures are necessary to achieve acceptable symptom reduction, and it is for that reason that it is very important to investigate the patients’ experience of treatment. In current literature, there is limited available evidence regarding patient experience, except for pain scores [6]. Therefore, it is of even greater importance to compare both treatments in other domains, with the use of the recently developed PROM-HISS questionnaire [11, 13].

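### Work leave is recorded at 6 months in the text but only up to 6 weeks in Table 2, and the single PREM supports conclusions about the first session only

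*Protocol article*

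**What the plan says.** **Work leave.** The Secondary outcomes section groups three items, number of treatments, crossover and work leave, and puts all of them at the end of follow-up: "days of work leave are recorded after a total of 6 months of follow-up". Table 2 marks number of treatments and crossover at 6 months. It marks absenteeism at 1 week and, in brackets, at 6 weeks. The bracket is not explained and the 6-month cell is blank. For the 6-month telephone call, the Participant timeline lists this content: "PROM questionnaire completed and (subjective) symptoms related to recurrence are assessed". Work leave is not named there.

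**Patient experience.** On the PREM, the Secondary outcomes section says: "The administration of this questionnaire takes place 1 week after treatment". The Participant timeline places it at the day 7 call, where "the PROM and PREM questionnaires are completed by the researcher". Table 2 marks it at 1 week only.

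**Repeat sessions.** Under Interventions, a second treatment follows after about 6–8 weeks, and a third or crossover treatment after a further interval of the same length. The Discussion says that one session is not enough for most patients and that, in most cases, "repeated procedures are necessary to achieve acceptable symptom reduction, and it is for that reason that it is very important to investigate" the experience of treatment.

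**The concern.** Sites building their forms from Table 2 and sites following the text would collect different work-leave variables. Under Table 2, the last scheduled entry falls before, or at the same visit as, the second session. Leave caused by second and later sessions would then go unrecorded. If the arms differ in the number of sessions needed, the arm needing more would look better on work leave than it is.

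The PREM raises a different issue. Its timing is consistent between the timeline and Table 2, but it does not match the stated reason for measuring experience. The items on undergoing the treatment again and recommending it are answered at day 7, before the patient knows whether the session worked or must be repeated. The abstract and Discussion nevertheless expect the trial to show which treatment patients experience as better overall.

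**Working it through.** **1. The plan's own figure.** The only design figure is the sample size. With 70% success in both arms, a 10-point margin, 2.5% in one tail and 80% power:

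n per arm = (1.960 + 0.842)² × 2 × 0.70 × 0.30 / 0.10² ≈ 7.85 × 42 ≈ 330, or 660 in total.

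This matches the article. It plays no part in the present point.

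**2. Schedules side by side.**

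| Outcome | Secondary outcomes text | Table 2: 1 week | Table 2: 6 weeks | Table 2: 6 months |
|---|---|---|---|---|
| Number of treatments | after 6 months | – | X | X |
| Crossover | after 6 months | – | – | X |
| Work leave / absenteeism | after 6 months | X | (X) | – |
| PREM | 1 week after treatment | X | – | – |

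The first two rows come from the same sentence as work leave and carry the 6-month mark. The blank for absenteeism is therefore unlikely to be an artefact of text extraction.

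**3. Timing of sessions against timing of collection.**
- Second session: about 6–8 weeks, that is, at or after the 6-week visit.
- Third or crossover session: 6 + 6 = 12 to 8 + 8 = 16 weeks.
- Last absenteeism entry under Table 2: 6 weeks, so leave following either repeat session comes later.
- 6-month call: about 26 weeks, which is 10 to 14 weeks after a third session given on this schedule. A cumulative question at that call would cover all three sessions.

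**4. Effect on the work-leave comparison.** Let m be the mean number of repeat sessions per patient in an arm and d the mean days of leave per repeat session. Under Table 2, the part of the between-arm difference that is lost is m(SCL) × d(SCL) − m(RBL) × d(RBL). It is zero if the arms match on this product. For equal d, the omission favours the arm with the larger m. The article gives neither m nor d, so no number can be attached.

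**5. Share of sessions without a PREM (illustration only).** Let r be the share of patients with a second session and t the share of those with a third. If the PREM covers the first session only:

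uncovered share = 1 − 1/(1 + r + r·t)

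| Assumed r | Assumed t | Uncovered share | Repeat sessions among 660 |
|---|---|---|---|
| 50% | 0% | 1 − 1/1.50 = 33% | 660 × 0.50 = 330 |
| 70% | 30% | 1 − 1/1.91 = 48% | 660 × 0.91 ≈ 601 |
| 90% | 50% | 1 − 1/2.35 = 57% | 660 × 1.35 = 891 |

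The values of r and t are assumptions. The article says only that most patients need more than one session.

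**The case against.** **Work leave.** A reader might infer that leave after repeat sessions is never counted. The article does not support that. It follows only if Table 2 overrides the text; if the Secondary outcomes section governs, the 6-month record captures it. Nor does the silence of the Participant timeline settle the matter in favour of Table 2, because its lists are not exhaustive. Its 6-month entry also omits number of treatments and crossover, which Table 2 marks there, and its day 7 entry omits absenteeism, which Table 2 marks at 1 week. In addition, number of treatments and crossover are reported outcomes, so an arm needing more sessions would show it there even if its leave were undercounted. All of this stands, and it makes the finding a contradiction rather than a demonstrated loss of data.

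**PREM.** The Secondary outcomes wording could mean after every treatment, and the anchor "baseline, 1 week, 6 weeks and 6 months after the first procedure" is stated for the primary outcome set. However, neither the timeline nor Table 2 provides a contact one week after a repeat session, so that reading would itself need a schedule change. A first-session PREM is also a sound measure: it precedes any crossover and compares the randomised procedures directly. The Discussion can be read as saying that a session's tolerability matters because sessions are often repeated. That defence stands for the measure, but not for extending its result to the whole course.

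**PROM-HISS satisfaction item.** Table 1 lists it among the primary outcomes, and the Primary outcomes section gives four time points for that set. The Treatment efficacy section mentions collection 1 week after the procedure, which leaves its 6-month use uncertain. In any case it does not measure procedural pain, urge, willingness to repeat or recommendation.

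**Conclusion.** The contradiction on work leave is real and should be reconciled. Whether data would be lost depends on which passage sites follow, and the article does not say. If Table 2 is followed, the bias on this outcome favours the arm needing more sessions; its size cannot be derived.

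The PREM as scheduled is a valid comparison of the first session. The weakness lies in drawing from it a conclusion about the treatment course, when the article itself expects most patients to have repeat procedures. A reader might infer that the 1-week PREM should give way to a course-level PREM at 6 months. The article does not support that step: it would add long recall of procedural pain and urge, and in crossover patients it would mix both procedures. A reader might also take a definite fraction of sessions to be uncovered. The 33% to 57% shown above rests entirely on assumed repeat rates, and it applies to work leave only if Table 2 governs.

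Only secondary outcomes are affected.

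**What to change.** 1. Reconcile the Secondary outcomes section, the Participant timeline and Table 2 on work leave. Add cumulative days of sick leave since the first treatment to the existing 6-month call, mark it in Table 2, explain or remove the bracket at 6 weeks, and name the 6-month total as the between-arm outcome.
2. Keep the 1-week PREM as the between-arm comparison and label it as first session. Then either limit the conclusion about which treatment patients experience as better to that session, or repeat the items on willingness to undergo the treatment again and to recommend it at 6 months as a supplementary measure. Ask these about the allocated treatment, so that they have a clear referent after crossover.
3. Take number and type of sessions from the CRF, not from the 6-month interview, because that caller is meant to be blinded.

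The cost is an edit to one table and the CRF, plus one to three questions at a call already planned. The downside is longer recall of sick leave; the 1-week and 6-week entries, if kept, can serve as a check.
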